## Serious Adverse Events SAE

1. Serious adverse event (SAE) is a medical event that occurs during the course of a clinical trial that requires hospitalization or prolonged hospitalization, is disabling, affects the ability to work, is life-threatening or death-threatening, or results in a congenital malformation. Includes the following unintended medical events: events that result in death; life-threatening events (defined as a subject being in danger of death at the time of the event); events that require hospitalization or extended hospitalization; events that can result in permanent or severe disability/insufficiency; and carcinogenicity or teratogenicity.
2. Drug exposure during pregnancy/lactation. In principle, pregnancy and lactation are inclusion exclusion criteria. If pregnancy occurs during the study, then the patient should be withdrawn from the study immediately, the investigator should be informed immediately, and the patient should be followed throughout the pregnancy and postpartum. The consequences should be documented even if both mother and child are completely normal without any adverse events. Even if the pregnancy is not an SAE, it should be reported using the SAE reporting form.
3. Disease progression (including signs and symptoms of progression) should not be reported as a Serious Adverse Event, but death due to disease progression should be reported as a Serious Adverse Event if it occurs within the trial or safety reporting period. Hospitalization for signs and symptoms of disease progression should not be reported as a Serious Adverse Event. If the final outcome of the cancer is death during the trial or safety reporting period, then the event leading to death must be reported as a serious adverse event.
4. Administering other antitumor therapy: If the subject is initiating other antitumor therapy, the reporting period for adverse events that are not deaths is up to the start of the new antitumor therapy. If the death occurs within the Serious Adverse Event Reporting Period after the end of study treatment, it must be reported regardless of whether the patient receives other treatment.
5. Hospitalization: Adverse events resulting in hospitalization or prolonged hospitalization in a clinical study should be considered serious adverse events. Any initial admission to a healthcare facility (even if shorter than 24 hours) meets this criterion. Hospitalization does not include the following: rehabilitation facilities, nursing homes, routine emergency room admissions, same-day surgery, hospitalizations or prolonged hospital stays not associated with a worsening of an adverse event that are not serious adverse events per se, (e.g., for the purpose of checking for abnormalities in laboratory tests that persisted to date prior to the trial);hospitalization for administrative reasons (e.g., routine annual physical examination); hospitalization mandated by the trial protocol during the clinical trial (e.g., performed as required by the trial protocol); elective hospitalization unrelated to the worsening of an adverse event (e.g., elective cosmetic surgery); scheduled treatments or surgeries that should have been documented throughout the trial protocol and/or in the individual subject's baseline data; hospitalization for the sole reason of blood product Admission for Use. Diagnostic or therapeutic invasive (e.g., surgery), non-invasive procedures should not be reported as adverse events. However, when the disease condition that led to the procedure meets the definition of an adverse event, it should be reported, e.g., acute appendicitis that developed during the adverse event reporting period should be reported as an adverse event, and the resulting appendectomy should be documented as the treatment for that adverse event.
6. Overdose: An overdose is defined as the addition of a trial medication by a subject within 24 hours (time adjusted to the specific protocol) at a dose higher than that prescribed by the investigator's physician. All trial drug overdoses should be reported as serious adverse events, whether or not they are related to an adverse event/serious adverse event.

## SAE's Reporting Procedures

Serious adverse events should be reported from the time the subject signs the informed consent form up to and including the 30th calendar day after the last dose of study drug. During the trial period, if a serious adverse event occurs, it must be reported to the clinical supervisor and the principal investigator within 24 hours, and at the same time fill in the "Serious Adverse Event (SAE) Report Form ", sign and date it.

All serious adverse events must be reported. Serious adverse events occurring more than 30 days after the last dose are generally not reported unless they are suspected to be related to the study drug.

Serious adverse events should be recorded in detail with symptoms, severity, time of occurrence, time of treatment, measures taken, and follow-up time and modality and regression. If the investigator believes that a serious adverse event is not related to the test drug but is potentially related to a study condition (e.g., termination of the original treatment, or comorbidities during the course of the trial), this relationship should be detailed in the narrative portion of the Serious Adverse Event page of the Medical Record Report Form. If the intensity of a particular ongoing serious adverse event or its relationship to the subject drug changes, a follow-up report of the serious adverse event should be sent immediately. All serious adverse events should be followed until recovery or stabilization.

# DATA COLLECTION AND DATA MANAGEMENT

## Data Auditing and Monitoring

Data entry and management is done by an independent data manager. For queries present in the case report form, the data manager will write a question answer form (DRQ) and send a query to the investigator through the clinical supervisor, who should answer and return as soon as possible, and the data manager will make data corrections, confirm and enter data based on the investigator's answers, and may send another DRQ if necessary.

## Database lockout

After data review and confirmation, the database are lockouted by the principal investigator, the statistical analyst. No further changes are made to the data files after locking.

## Statistical Analysis of Data Sets

Full Analysis Set (FAS): the efficacy of all cases enrolled and using the drug at least once was analyzed according to the principle of Intentional Analysis (ITT).

Efficacy Analysis Set (EAS): Patients who patients who received at least one dose of study drug and had at least one post-treatment tumor evaluation constituted the evaluable analysis set (EAS) population.. The efficacy of the drugs was statistically analyzed by both FAS and PPS.

Safety Analysis Set (SAS): all enrolled cases, all patients who have used the trial drug at least once and have a post-dose safety record. This data set is used for safety analysis.

## Statistical analysis plan

The results of this trial were mainly described statistically. Continuous data are presented with mean, standard deviation, median, maximum, and minimum values, while count data and ordinal data are presented with frequency (percentage), rate, and confidence interval. All statistical analyses will be programmed and calculated using SAS 9.3 statistical analysis software OR R version 3.4.1. All statistical tests will be two-sided, with a p-value less than or equal to 0.05 being considered statistically significant, and 95% confidence intervals will be used for the differences tested.

Basic patient characteristics are presented with mean, standard deviation, median, maximum and minimum values for quantitative data, and frequencies and percentages were listed for qualitative data.

Efficacy analysis: median PFS and its 95% CI were calculated using the kaplan-Meier method and their survival graphs were plotted for comparison. For secondary efficacy indicators, the kaplan-Meier method was used to estimate the median OS and its 95% CI, and survival graphs were plotted. Objective remission rate (ORR=CR+PR) and disease control rate (DCR=CR+PR+SD) were calculated and their 95% CIs. Quality of life scores were compared with baseline values using paired t-tests or signed rank-sum tests to compare the before-and-after differences within groups.

Safety evaluation: descriptive statistical analysis is the main focus, the table describes the adverse events and adverse reactions that occurred in this trial. (where an adverse reaction is defined as “an adverse event that is 'definitely related/highly likely related/possibly related' to the study drug”) Laboratory test results describing pre-test normal but post-treatment abnormalities and the relationship to the test drug when abnormal changes occurred.

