# STUDY ENPOINTS

## Primary Endpoints

- Safety (per CTCAE 5.0 criteria)

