# SUBJECT SELETION

## Inclusion Criteria

1. Pathologically confirmed extensive stage small cell lung cancer;
2. Extensive small cell lung cancer (per the Veterans Administration
3. Lung Study Group (VALG) staging system) not receiving systemic treatment;
4. Received prior surgery and adjuvant therapy for curative intent such as radiotherapy and chemotherapy; at least 6 months of treatment-free period since last chemotherapy, radiotherapy, or chemoradiotherapy to diagnosis of extensive-stage SCLC;
5. Measurable lesions according to Response Evaluation Criteria in Solid Tumors (RECIST) version 1.1;
6. Male or female ≥ 18 years of age and ≤ 75 years of age;
7. ECOG performance status score of 0-1;
8. Life expectancy ≥ 12 weeks;
9. Adequate organ system function (excluding the use of any blood components and cell growth factors during screening):
   1. Hemoglobin ≥ 9 g/dL
   2. Absolute neutrophil count ≥1.5×109/L
   3. Platelets ≥100 × 109/L
   4. Serum albumin ≥ 3/dL
   5. Total bilirubin ≤ ULN
   6. ALT and AST ≤ 1.5 × ULN; AKP ≤ 2.5 × ULN
   7. Serum creatinine ≤1.5 ULN or creatinine clearance(CrCl) ≥60 mL/min (Cockcroft -Gault formula). Negative urine protein or 24-hour urine protein quantification <1.0 g
   8. Thyroid stimulating hormone (TSH) ≤ULN (subjects with normal T3 and T4 levels are allowed to be enrolled although TSH＞ULN)
10. Contraception (e.g., IUD, contraceptives, or condoms); a negative pregnancy test within 7 days prior to enrollment for women of childbearing age;
11. Subjects voluntarily enrolled in this study and signed an informed consent form.

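### The one laboratory summary named in section 14.4 covers only normal-to-abnormal changes, so worsening in subjects enrolled with abnormal baselines is seen only if it is also reported as an adverse event

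*Protocol*

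**What the plan says.** The safety paragraph of protocol section 14.4 plans two outputs. In the first, "the table describes the adverse events and adverse reactions that occurred in this trial". The second is a laboratory summary: "Laboratory test results describing pre-test normal but post-treatment abnormalities and the relationship to the test drug when abnormal changes occurred". No other laboratory display is named.

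Inclusion criterion 9 (section 5.1, repeated in the Abstract) sets the laboratory limits for entry. They include "Hemoglobin ≥ 9 g/dL", "ALT and AST ≤ 1.5 × ULN; AKP ≤ 2.5 × ULN", "Serum creatinine ≤1.5 ULN or creatinine clearance(CrCl) ≥60 mL/min" and "Negative urine protein or 24-hour urine protein quantification <1.0 g". TSH above the upper limit of normal is allowed when T3 and T4 are normal. Total bilirubin must not exceed the upper limit of normal.

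Section 2.1 makes safety by CTCAE 5.0 the sole primary endpoint. The safety analysis set in section 14.3 is all enrolled subjects with at least one dose and a post-dose safety record; it has no condition on baseline laboratory values.

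**The concern.** The laboratory summary and the entry criteria do not fit together. The summary requires a normal starting value, while the criteria deliberately admit subjects without one on several tests. For those subjects and tests, no degree of worsening can satisfy the stated condition.

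Safety is the primary endpoint and the trial has a single arm. The laboratory results will therefore be read on their own, as a description of how the regimen is tolerated. A summary that omits part of the safety set for some tests, without saying so, can make laboratory toxicity look milder than it was. As worded, it also separates normal from abnormal without using grades, although the endpoint is defined by CTCAE grade.

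**Working it through.** The protocol gives no figure to reproduce here. The check sets the summary's condition beside each entry limit, then follows the other route by which a worsening could reach the results.

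**Step 1. Which tests can have an abnormal baseline (inclusion criterion 9)?**

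| Test | Entry limit | Abnormal baseline possible? |
| --- | --- | --- |
| ALT, AST | up to 1.5 × ULN | Yes |
| AKP | up to 2.5 × ULN | Yes |
| Creatinine | up to 1.5 × ULN, or qualify on clearance | Yes |
| Urine protein | not negative, if under 1.0 g in 24 hours | Yes |
| TSH | above ULN, if T3 and T4 normal | Yes |
| Hemoglobin | 9 g/dL or more | By assumption; no normal range is given |
| Total bilirubin | no higher than ULN | No |

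**Step 2. Apply the condition.** The summary needs a normal value before and an abnormal value after treatment. A subject who enters with ALT at 1.4 × ULN and later reaches Grade 3 fails the first half and is absent from the ALT summary. The same holds for the other four tests marked Yes without qualification.

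**Step 3. Follow the adverse event route.**
- Section 13.2 lets an abnormal laboratory result be an adverse event and does not require a normal baseline.
- The notes to Tables 7 and 9 have laboratory tests assessed by CTCAE v5.0 alongside adverse events.
- Section 13.4 sends abnormal laboratory data to the case report form.

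A worsening from an abnormal baseline can therefore reach the adverse event table. None of these places says when a laboratory change must be reported as an adverse event. The ECG text in section 13.1.2 does have such a rule: a clinically significant abnormality is to be documented as an adverse event. Laboratory tests have no counterpart, so capture depends on the investigator's judgement.

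**Step 4. Scale.** The protocol plans 36 subjects (section 4) and gives no share with abnormal baselines. Taking 10% to 50% for a given test as an assumption:
- lower end: 0.10 × 36 = 3.6, about 4 subjects;
- upper end: 0.50 × 36 = 18 subjects.

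These are subjects who could not appear in the summary for that test, whatever happened to them. They are not counts of missed toxicities.

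**The case against.** **The adverse event table covers it.** A reader might infer that worsening from an abnormal baseline is left out of the primary safety analysis. The protocol does not support that: the table in section 14.4 has no baseline condition, and laboratory abnormalities can be adverse events. The dose-adjustment tables also tie treatment actions to laboratory grades or counts, and section 9.1 requires the reasons for adjustments to be documented, so severe changes are unlikely to go unnoticed. This stands, and it limits the point to the laboratory summary. It does not close the gap, because noting a value or a dose change in the case report form does not by itself make it an adverse event.

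**The text excludes no other display, and output detail belongs in a statistical analysis plan.** It is true that the protocol names one summary without ruling out others, and that a separate plan, not shown, may add shift tables. But the point concerns a condition that the protocol states, not a missing detail. A plan that follows the sentence inherits the condition.

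**The wording is loose.** The clause on relationship to the drug could be read as covering any abnormal change. The more natural reading carries the normal-baseline condition through the sentence. If the wider reading is meant, the text should say so.

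**The size.** A reader might try to quantify the bias. If 40% had abnormal baselines, with Grade 3 or higher risks of 20% (normal baseline) and 40% (abnormal baseline), the overall rate would be 0.6 × 0.20 + 0.4 × 0.40 = 28%, against 0.6 × 0.20 = 12% visible. None of these inputs is in the protocol. The stated summary is ungraded, so it yields no Grade 3 rate. Its denominator is not given: among normal-baseline subjects the same inputs give 20%. The contrast also treats adverse event capture as zero. It should not be used.

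**Conclusion.** The point holds for the laboratory summary. As worded, it cannot show worsening in subjects who enter with abnormal ALT/AST, AKP, creatinine, urine protein or TSH. Hemoglobin probably belongs with them, on the assumption that values just above the entry floor are below normal; bilirubin does not. For these subjects, worsening up to Grade 3 or 4 reaches the safety results only through adverse event reporting, for which no laboratory rule is given.

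The size of any understatement cannot be derived from the protocol. The figure of about 4 to 18 of 36 subjects per test rests wholly on the assumed 10% to 50% with abnormal baselines. This should be corrected because safety is the primary endpoint, but it does not invalidate the primary analysis.

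**What to change.** Replace the laboratory sentence in section 14.4 with one to this effect: for each CTCAE-gradable laboratory parameter, in all subjects of the safety analysis set, tabulate the shift from baseline CTCAE v5.0 grade to worst post-baseline grade, with the number and percentage worsening by at least one grade and the number and percentage worsening to Grade 3 or higher. Any parameter without a CTCAE grade can be summarised by change from baseline.

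A rule in section 13 on when a worsening from an abnormal baseline is recorded as an adverse event, parallel to the ECG rule, would close the other half of the gap.

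The cost is one sentence and standard table programming. Screening and on-treatment laboratory values are already scheduled, so no new data are needed. The downside is that reported laboratory toxicity may look less favourable.

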# MEDICINES MANAGEMENT

The management, distribution and recovery of the drugs used in this clinical trial are under the responsibility of specialized personnel, and the test drugs should be sealed, protected from light, and stored at the proper temperature. The investigator must ensure that all test drugs are used only for the subjects participating in the clinical trial, and their dosage and usage should follow the trial protocol, and the remaining drugs are returned to Jiangsu Hengrui Pharmaceutical Co., Ltd. and the test drugs for clinical use shall not be transferred to any non-clinical trial participants.

When the drug is distributed, a drug receipt form shall be signed, double signed, in duplicate, one for each of the clinical research unit and Jiangsu Hengrui Pharmaceutical Co. At the end of the study, the remaining drugs and empty boxes will be collected. Both parties shall sign the drug recovery form. The issuance and recovery of each drug shall be recorded in a timely manner on a special record sheet. Supervisors are responsible for supervising the process of supplying, using, storing and disposing of the remaining drugs used in the clinical trial.

Upon written notification to the Co-organizer, the investigator may destroy used drug products and empty cartridges, provided that the health of the population is not jeopardized. The investigator should maintain records of the disposal of all trial medications. These records must show the certification and quantity of drugs destroyed in each batch, as well as the method of disposal (in accordance with the requirements of local law), and the person who disposed of the drugs.

# ETHICAL CONSIDERATIONS

The study was conducted in strict compliance with the ethical guidelines for human medical research of the Declaration of Helsinki and Chinese clinical trial regulations. Prior to the commencement of the study, the protocol and subject informed consent forms were reviewed and approved by the PI unit and the Ethics Committee prior to the commencement of the study.

During the study period, it was strictly ensured that all operations were carried out in accordance with the approved protocols During the implementation process, any modification of the study protocols had to be re-submitted to the Ethics Committee for consent, and the occurrence of severe adverse events was reported to the Hospital Ethics Committee.

Before each subject was enrolled in this study, a complete, comprehensive and truthful description of the purpose, steps and possible risks, benefits and related rights and interests of the study was given to the affected person or his/her designated representative in written text, to ensure that each subject voluntarily participated in this experimental study and signed a written informed consent form, so that the subject's rights were fully protected, and that all the subject's information was kept strictly confidential.

The study has registered in the Chinese Clinical Trial Registry with NCT05001412.

# STUDY PLAN

- 2020.9 - 2021.1 Submissions, Ethical Review of Research Units.
- 2021.2-2022.2 The patients were enrolled and the data were recorded.
- 2022.3-2023.03 Complete follow-up and data collection of all enrolled patients.
- 2023.04-2024.12 Data analysis, paper writing and contributions.

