The two immune checkpoint inhibitors currently approved for broad-stage small cell lung cancer indications are both PD-L1 antibodies. 2020 ASCO reported updated data on two PD-1 antibodies, Nivolumab and Pembrolizumab, in first-line combination chemotherapy. The primary endpoint of PFS was achieved with Nivolumab in combination with CE versus CE chemotherapy, with a median PFS of 5.5 months versus 4.7 months, HR=0.68, p=0.047, and a statistically significant difference of 0.8-month. Unfortunately, the secondary endpoint of OS was not achieved in the modified study, with a median OS of 11.3 months versus 9.3 months ,p=0.14, which was not statistically significant. The Keynote-604 study also did not provide a positive OS result for first-line combination chemotherapy with pembrolizumab, although the median OS was 10.8 months versus 9.7 months, with a P-value of 0.0164, which did not meet the efficacy cutoff of 0.0128, and was therefore not statistically different. statistical difference^5^ .

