**Figure 1. Study Flow Chart**

# SAMPLE SIZE

The study plans to enroll 36 subjects.

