## Secondary Efficacy Indicators

- Progression-free survival (PFS)：PFS was determined as the interval from initiation of the study dose to disease progression or death, whichever occurred first.
- Overall survival (OS): OS was determined as the interval from initiation of the study dose to death from any cause.
- Overall survival (ORR): ORR was determined as the percentage of patients who had complete response (CR) or partial response (PR) as best overall response per RECIST v1.1.
- Disease control rate (DCR): DCR was defined as the percentage of patients with CR, PR or SD. DoR was determined as the interval from the initial documented objective response to disease progression or death from any cause.

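### All follow-up ends 13 months after the last enrolment, so the 95% CI for median OS may lack an upper limit; continuing survival contacts into the 21 months set aside for analysis would largely cure this

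*Protocol*

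**What the plan says.** Section 17 (Study Plan) sets the calendar, and the Abstract repeats it:

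- Enrolment: "2021.2-2022.2 The patients were enrolled and the data were recorded".
- Follow-up: "2022.3-2023.03 Complete follow-up and data collection of all enrolled patients".
- Remaining time: "2023.04-2024.12 Data analysis, paper writing and contributions".

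Section 4 gives the sample size ("The study plans to enroll 36 subjects") with no target median, precision or number of deaths. Section 12.2 defines the endpoint: "OS was determined as the interval from initiation of the study dose to death from any cause". Section 14.4 states the analysis: "the kaplan-Meier method was used to estimate the median OS and its 95% CI". It does not name the interval transform; on software it says only "All statistical analyses will be programmed and calculated using SAS 9.3 statistical analysis software OR R version 3.4.1".

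The Schedule of Activities and Table 10 provide for survival contact every three months after treatment. Neither gives a stop date, a required number of deaths or a minimum follow-up, so section 17 is the only place that ends OS follow-up.

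For small-cell disease, section 1 quotes nivolumab plus chemotherapy "with a median OS of 11.3 months versus 9.3 months", pembrolizumab plus chemotherapy at 10.8 versus 9.7 months, and camrelizumab plus apatinib at 8.4 months.

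**The concern.** A confidence interval for a Kaplan-Meier median has an upper limit only if the upper confidence band itself falls to 0.5. With 36 subjects the curve has to fall well below 0.5 for that, which takes both time and deaths. The calendar stops collecting deaths 13 months after the last entry.

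Section 1 calls PD-1 plus chemotherapy unsatisfactory and asks whether an anti-angiogenic drug improves on it. OS above the quoted 10.8 to 11.3 months is therefore the result the trial hopes to see, and it is where the upper limit becomes least likely to exist. In a single-arm study read against outside figures, the interval is the reader's main guide to how firm the median is. Meanwhile, 21 months are set aside in which no survival follow-up is listed.

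**Working it through.** **Calendar.** End of February 2022 to end of March 2023 is 13 months. Enrolment from February 2021 to February 2022 spans 13 months, so the longest possible follow-up is 13 + 13 = 26 months and the shortest is 13. April 2023 to December 2024 is 9 + 12 = 21 months. A cut-off at end of March 2024 falls 25 months after the last entry, giving 25 to 38 months per subject.

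**Assumptions not in the protocol.** Uniform entry, exponential OS, no loss to follow-up, and the true median. The protocol gives no precision target for its 36 subjects, so there is no stated figure to reproduce.

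**How far the curve must fall.** Ignoring censoring, the upper band reaches 0.5 when S + 1.96 × √(S(1 − S)/36) = 0.5. At S = 0.345 this is 0.345 + 1.96 × 0.0792 = 0.500. An exponential curve with median m reaches 0.345 at m × ln(1/0.345)/ln 2 = 1.535 m. The share of subjects whose possible follow-up at 2023.03 extends to that time is (26 − 1.535 m)/13:

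- m = 11.3: 17.3 months, share 67%.
- m = 13: 20.0 months, share 46%.
- m = 15: 23.0 months, share 23% (about 8 of 36).

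With a 2024.03 cut-off every subject could be followed for at least 25 months, so the share is 100% in all three cases.

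**Expected deaths.** With λ = ln 2/m and minimum follow-up f, deaths = 36 × {1 − [exp(−λf) − exp(−λ(f + 13))]/(13λ)}. For m = 15, λ = 0.0462:

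- f = 13: 36 × {1 − (0.5484 − 0.3007)/0.6007} = 21.2.
- f = 25: 36 × {1 − (0.3150 − 0.1727)/0.6007} = 27.5.

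**Simulation at 2023.03.** 36 subjects, at least 10,000 runs per case in the main simulation. With g the square root of Greenwood's sum Σ d/[r(r − d)], the upper band is S^exp(−1.96 g/|ln S|) for log-log and S × exp(1.96 g) for log. The limit counts as missing if the band never falls to 0.5.

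| True median (months) | Expected deaths | Median not reached | Upper limit missing, log-log | Upper limit missing, log |
|---|---|---|---|---|
| 11.3 | 24.8 | 0.2% | 17% | 43% |
| 13 | 23.0 | 1% | 36% | 68% |
| 15 | 21.2 | 5% | 59% | 84% |
| 18 | 18.8 | 16% | 80% | 94% |

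Repeat simulations move these percentages by one or two points.

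**Sensitivity at 2023.03 (log-log).**

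- Weibull shape 1.3: 4% at 11.3 months, 16% at 13, 39% at 15.
- Loss to follow-up of 10% a year: 42% at 13, 61% at 15.
- Twelve instead of 13 months after the last entry: 64% at 15.

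**Cut-off 2024.03.** The upper limit is missing (log-log / log) in about 0.1% / 1% at 11.3 months, 4% / 13% at 15 and 19% / 42% at 18.

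**The case against.** Several objections have force.

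- **The OS result does not fail.** A reader might infer that the promised analysis breaks down. It does not: the median is reached in about 95% of trials at 15 months, and a median with a finite lower limit and an upper limit reported as not estimable is a valid result.
- **The cut-off is not adequate only at benchmark survival.** That inference is also too strong. At 13 months the upper limit still exists in about 64% of trials with log-log intervals, and in 84% with Weibull shape 1.3. It is missing in most trials only from about 15 months under exponential survival, or earlier with log intervals.
- **The longer medians are assumptions.** The protocol sets no OS target, so no stated design assumption is contradicted. The 14.7 and 19.5 months in section 1 concern non-small-cell disease and are not benchmarks here.
- **The stakes are modest.** Safety is the primary endpoint, OS is one of five secondary endpoints, and no hypothesis test or decision depends on the upper limit.
- **Section 17 is a calendar, not a censoring rule.** The three-monthly contacts have no stop date, and an analysis plan could set a later OS cut-off. This only partly answers the point. Section 17 expressly ends follow-up and data collection for everyone enrolled in 2023.03, and an analysis plan cannot supply deaths that were not collected.

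A reader might also want to move DoR to the later cut-off. Survival contacts do not support that: under section 12.2 DoR ends at progression or death, and progression is found by imaging.

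**Conclusion.** The point stands as a matter of precision. The dates fix 13 to 26 months of follow-up. At the best quoted small-cell benchmark, the upper limit of the OS interval is missing in about one trial in six (log-log) or more than two in five (log), and the risk rises steeply if the regimen does better. The size depends on the true median, the survival shape, uniform entry and the interval transform, none of which the protocol fixes. The direction holds across the ranges examined. The median itself will usually be available and no error rate is affected, so this is a worthwhile and inexpensive improvement, not a defect that invalidates the plan.

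**What to change.** Amend section 17, its copy in the Abstract, and section 14.4 so that the three-monthly survival contacts already scheduled continue to about 2024.03 and the final OS analysis uses that cut-off. Keep safety, ORR, DCR, PFS and DoR at 2023.03. Amend section 14.2, which allows no changes once the database is locked, to permit a separate later lock of the OS data.

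The cost is about four more contact rounds (12 months ÷ 3) for subjects still alive: 36 − 21 = 15 expected at 2023.03 if the median is 15 months, so at most about 60 contacts. There is also a second lock, and the final OS result comes about a year later. No new subjects or procedures are needed, and nine months remain before the plan's 2024.12 end date.
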